### Patient information

The patient will be included after the call centre’s physician has obtained the caller’s informed consent. The patient will be sent an information sheet by mail.

### Pilot study

A pilot study of 570 calls conducted from January to June 2011 at the Seine-Saint-Denis call centre demonstrated the feasibility of caller recruitment and of patient follow-up by telephone. The percentage of refusals-to-participate and lost-to-follow-up was 15 %.

### Sample size

We postulate that fTMA will reduce the percentage of out-of-hours on-duty GP consultations or the number of visits to an ED during the 2 weeks following the index call. In the study by Lattimer et al., the percentage of hospital admissions and ED visits was 12 % after a nurse telephone consultation [17]. In a parallel study, Thompson et al. reported a 21 % versus a 33 % overnight call rate resulting in a home visit by a duty GP in the nurse telephone intervention arm versus the control arm [18]. We estimate that the percentage of out-of-hours consultations and ED visits (our primary endpoint) will be 50 % in the control group. We aim for an absolute reduction of at least 10 % (i.e. from 50 to 40 %) in the intervention arm for each indication (fever/gastroenteritis).

On the assumption of a relatively low weak design effect due to cluster randomisation (about 1.5), and considering a loss of follow-up of 15 %, it is estimated that a sample size of 663 patients/arm/indication will be required for 85 % power and a 5 % alpha risk. If account is taken of an attrition rate of about 8 %, 720 patients will be required (1440/indication, i.e. a total of 2880 patients). This sample size should provide enough power and precision for subgroup analyses (season versus diurnal cycle, weekend versus weekdays).

Inclusions will take place over a full year in order to obtain a representative sample. Each centre will thus include about 240 patients for each indication. A random sample of four patients per week will be drawn outside of an epidemic (about 42 weeks) and of eight patients per week during an epidemic (about 10 weeks) in each centre for each indication. For feasibility reasons, the first patient whose call is closest to the dates and times that will have been randomly drawn for each week of the year of study will be included for each indication.

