## Methods/design

### Design

This is a prospective open-label, multicentre, pragmatic, cluster randomised clinical trial involving six participating centres (SAMU). The centres are randomised into two arms (1:1) according to call management method, either an offer of fTMA (intervention arm) or usual after-hours medical care (control arm). Out-of-hours is 8 p.m. to 7.59 a.m. on weekdays, 1 p.m. to 7.59 a.m. on Saturdays and round-the-clock on Sundays and school holidays. Callers/patients will be randomly selected before inclusion (see Fig. 1 for the study flowchart).

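### The stated 85% power rests on a normal critical value; with six centres randomised three against three, a test that holds the 5% level has about 62% power at the plan's own design effect

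*Protocol article*

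**What the plan says.** The Design section of the protocol article names six participating call centres as the randomised units: "The centres are randomised into two arms (1:1"), which gives three centres per arm.

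The Sample size section expects that the primary endpoint "will be 50 % in the control group", and aims for an "absolute reduction of at least 10 % (i.e. from 50 to 40 %) in the intervention arm for each indication". It proceeds "On the assumption of a relatively low weak design effect due to cluster randomisation (about 1.5") and "considering a loss of follow-up of 15" per cent, and concludes that "a sample size of 663 patients/arm/indication will be required for 85 % power and a 5 % alpha risk". It continues: "If account is taken of an attrition rate of about 8 %, 720 patients will be required". On recruitment per centre it says: "Each centre will thus include about 240 patients for each indication".

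The Statistical analyses section tests the primary endpoint with a GEE model that allows for the clustering, two-sided at 5%. It also says that intracluster correlation coefficients will be calculated. The article gives no numerical intracluster correlation and does not say which reference distribution the sample size used.

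**The concern.** A design effect corrects the variance for clustering. It does not correct for the fact that the between-centre variance must be estimated from very few centres. With three centres per arm, that second problem is large. A critical value of 1.96 would be right if the between-centre variance were known in advance, but here it is to be estimated from the trial.

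Two errors of interpretation are at stake, and which one arises depends on the test finally used. If the test is corrected for six clusters, a non-significant result could be read as strong evidence against a 10-point reduction because the trial was said to have 85% power. If GEE is run with uncorrected robust standard errors, the apparent power is high but the 5% level is not held, and the hazard is a false positive.

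**Working it through.** **Inputs from the article.** Control rate 0.50, intervention rate 0.40, design effect (DE) 1.5, 663 per arm per indication, raised to 720 for 8% attrition, about 240 per centre per indication, 15% loss to follow-up (Sample size); six centres, 1:1 (Design); two-sided 5% (Statistical analyses). Equal centre sizes are assumed throughout.

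**1. The plan's own figure.** The usual two-proportion formula with pooled variance, 85% power and two-sided 5% gives 443 per arm; 443 × 1.5 = 664.5. The unpooled formula gives 440 × 1.5 = 660. Both agree with 663. Conversely, 663 / 1.5 = 442 effective patients per arm gives a normal-approximation power of about 85%. Also 663 / 0.92 = 721, against the stated 720. So the plan used a normal critical value. The 15% loss does not enter 663: including it would give 664.5 / 0.85 = 782. This is why 612 (720 × 0.85) is shown below beside 663 and 720.

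**2. Implied intracluster correlation (ICC).** DE = 1 + (m − 1) × ICC, so ICC = 0.5 / (m − 1): 0.0021 for m = 240, 0.0023 for m = 221 (663 / 3), 0.0025 for m = 204 (612 / 3).

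**3. Power on 4 degrees of freedom.** Six centres less two arm means leave 4 df; the critical value is 2.776. SE = √[(0.25 + 0.24) × DE / n], noncentrality = 0.10 / SE, and power comes from the noncentral t distribution.

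| Analysed per arm | SE at DE 1.5 | Noncentrality | Power, DE 1.5 | Power, DE 1.0 |
|---|---|---|---|---|
| 612 | 0.0347 | 2.89 | 59% | 75% |
| 663 | 0.0333 | 3.00 | 62% | 78% |
| 720 | 0.0320 | 3.13 | 65% | 81% |

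The last column shows that the shortfall does not depend on a disputed ICC: on 4 df, 85% is missed even with no clustering.

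**4. Check by simulation.** Beta-binomial data, three centres against three, 221 patients each, ICC 0.0023, 200,000 runs. A t-test on centre proportions had type I error 4.9% and power 62.0%. An uncorrected sandwich variance on the same proportions, referred to 1.96, rejected about 90% of the time under 50% against 40%, and about 18% of the time under no difference.

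**5. Sensitivity on one n (612 per arm, 204 per centre, 4 df).** The ICCs from 0.005 upwards are illustrative; the article gives none. The detectable difference d has 85% power, which needs a noncentrality of 4.04. It solves d = 4.04 × √[(0.25 + (0.5 − d)(0.5 + d)) × DE / n], so the variance matches the alternative.

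| ICC | DE | Power for 10 points | Detectable difference |
|---|---|---|---|
| 0.0025 (DE as planned) | 1.50 | 59% | 13.9 points |
| 0.005 | 2.02 | 47% | 16.0 points |
| 0.01 | 3.03 | 34% | 19.3 points |
| 0.02 | 5.06 | 23% | 24.4 points |
| 0.05 | 11.15 | 13% | 33.9 points |

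At DE 1.5 the detectable difference is 13.3 points with 663 per arm and 12.8 with 720.

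**The case against.** **The analysis plan may settle the test.** The article names only GEE, and a small-sample correction is commonly left to an analysis plan, which is not at hand. It is fair that the 4-df reference is an assumption of this review, and the absence of a named correction is not the point here. The point is a stated power. A correction would restore the 5% level but not the 85%; without one, the 5% level in the same sentence is not met. Neither route delivers both.

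**The calculation is consistent on its own terms.** It is: step 1 reproduces it. What fails is the step from 442 effective patients to a normal test when six units are randomised.

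**Which n is right is uncertain.** This stands. The pilot's 15% combines refusals with loss to follow-up, and refusers are never included, so 612 may be pessimistic; 720 assumes that every outcome is known. Hence the range of 59 to 65%.

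**Stronger readings that the article does not support.** A reader might infer that true power is 13 to 47% because a design effect of 1.5 is too low. It implies a between-centre SD of only √(0.0021 × 0.25) = 0.023, or 2.3 points, but nothing in the article shows the real ICC to be larger. That no source is cited counts for little in an article that condenses a fuller protocol. A reader might also infer that extra patients in the same centres would hardly help. At ICC 0.01, doubling 612 raises power only from 34% to about 40%, but at the plan's own ICC of 0.0021 it raises it from about 61% to about 78%.

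**Recruitment has closed.** Inclusion ended in July 2016, so restating power changes neither conduct nor the estimate. Its value lies in how the result is read.

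**Conclusion.** The concern holds. Under the protocol's own effect size and design effect, 85% power at a true two-sided 5% level is not delivered. On about 4 between-centre degrees of freedom, power per indication is about 62% at 663 analysed per arm, with a range of 59% (612) to 65% (720). The shortfall is thus roughly 20 to 26 percentage points, and some of it remains at any ICC of zero or above.

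This rests on equal centre sizes and a test with about 4 df. The Discussion section reports enrolment difficulties in two centres; unequal sizes would lower power further.

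It would go too far to say that a non-significant result could never exclude a 10-point reduction. At DE 1.5 and 663 per arm the expected 95% half-width is 2.776 × 0.0333 = 0.092, or 9.2 points, so an estimate near zero could just exclude it. Non-significance by itself does not.

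**What to change.** In the Sample size section, or in an addendum before the primary analysis:

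- Withdraw the 85% figure and state power per indication as about 59 to 65% for three centres against three, on 4 df, at a design effect of 1.5.
- Add the table from step 5 on one consistent n, with the ICCs labelled as illustrative and the detectable differences computed with a variance that matches the alternative.
- State that the primary result will be judged by a confidence interval that is valid for six clusters, and that a non-significant result does not by itself exclude a 10-point reduction.

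No additional patients or centres are asked for. The cost is a rewritten paragraph and a less favourable stated power.

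### The 663 per arm per indication cannot hold a design effect of about 1.5, 15 % loss to follow-up and 85 % power together; 720 enrolled gives 85 % power only if total loss is about 8 %

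*Protocol article*

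**What the plan says.** All of the design figures are in the Sample size section of the protocol article, except where noted.

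- Control rate: "our primary endpoint) will be 50 % in the control group".
- Effect: an "absolute reduction of at least 10 % (i.e. from 50 to 40 %) in the intervention arm for each indication".
- Clustering: a "relatively low weak design effect due to cluster randomisation (about 1.5").
- Result: "and considering a loss of follow-up of" 15 %, "it is estimated that a sample size of 663 patients/arm/indication will be required", at 85 % power and 5 % alpha.
- Next step: "If account is taken of an attrition rate of about" 8 %, the number becomes 720 per arm per indication, hence 1440 per indication and 2880 in all.

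The Statistical analyses section makes all tests two-tailed, and the Design section allocates centres 1:1. The Pilot study section reports one combined figure: "The percentage of refusals-to-participate and lost-to-follow-up was" 15 %. Under Data collection, inclusion takes effect only once the caller has agreed to data collection and to the follow-up call.

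**The concern.** As worded, 15 % loss is already inside 663, and a further 8 % is added to reach 720. A reader would conclude that the trial keeps 85 % power with 15 % of patients lost, and has a margin beyond that. The arithmetic does not support this.

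This paragraph is the only justification given for the size of the primary comparison in each indication, and it also claims enough power for subgroup analyses. It names two kinds of loss, 15 % and 8 %, without saying how they differ. The reader therefore cannot tell what level of loss the enrolled number was meant to withstand.

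**Working it through.** **Inputs.** p1 = 0.50, p2 = 0.40, power 0.85, design effect 1.5, loss 0.15 and attrition 0.08 (Sample size); two-sided alpha 0.05 (Statistical analyses); 1:1 allocation (Design). z(0.975) = 1.960 and z(0.85) = 1.036.

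**1. Base size per arm, individual randomisation.**
- Unpooled variance: (0.25 + 0.24)(1.960 + 1.036)² / 0.10² = 439.9.
- Pooled variance under the null: (1.960·√(2·0.45·0.55) + 1.036·√(0.25 + 0.24))² / 0.10² = 442.9.

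**2. Reproducing 663.**
- Design effect only: 439.9 × 1.5 = 659.9; 442.9 × 1.5 = 664.3. The stated 663 lies between them, and 442 × 1.5 = 663.
- Design effect and 15 % loss: 659.9/0.85 = 776; 664.3/0.85 = 782. The stated 663 is about 15 % below this.
- With a continuity correction the base is 463, and 463 × 1.5/0.85 is about 818, which is further away.
- For 663 to contain the 15 % loss, the design effect would have to be 663 × 0.85/443 = 1.27.
- Another route to the same figure: two-sided 80 % power, unpooled, gives a base of 384.6, and 384.6 × 1.5 × 1.15 = 663.4. Here the loss is inside 663, as a multiplier, but the power is not 85 %.

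No two-sided 85 % variant tried (pooled, unpooled, continuity-corrected, arcsine) gives 663 with both the design effect and the 15 % loss.

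**3. From 663 to 720.** 663/0.92 = 720.7 and 720 × 0.92 = 662.4. This step adds about 8 % and nothing more.

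**4. Power with 720 enrolled per arm per indication.** Effective n = evaluable n/1.5. Power = Φ[(0.10·√n − 1.960·√0.495)/√0.49].

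| Loss assumed | Evaluable | Effective | Power |
|---|---|---|---|
| 8 % | 662 | 442 | 84.9 % |
| 10 % | 648 | 432 | 84.1 % |
| 12 % | 634 | 422 | 83.3 % |
| 15 % | 612 | 408 | 82.0 % |
| 15 % and then 8 % | 563 | 375 | 78.8 % |

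These powers do not depend on how 663 was originally derived.

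**The case against.** **The shortfall is small against the looseness of the inputs.** The design effect is given only as about 1.5. At 15 % loss, a value of 1.4 gives 84.5 % power and 1.38 (612/443) restores 85 %. With 240 patients per centre per indication, 1.5 and 1.38 correspond to intracluster correlations of 0.5/239 = 0.0021 and 0.38/239 = 0.0016, and nothing in the article separates these. Loss also makes the clusters smaller. If 1.5 belongs to 663/3 = 221 evaluable patients per centre, the correlation is 0.5/220 = 0.0023. At 612/3 = 204 per centre the design effect is then 1 + 203 × 0.0023 = 1.46, and power is 83.0 %. All this stands as a limit on the size of the problem. It does not make 663 agree with the inputs stated for it.

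**True loss may be below 15 %.** The pilot's 15 % combines refusals with losses, and refusals come before inclusion, so they need no inflation of the enrolled number. If loss after inclusion is near 8 %, 720 delivers the stated power. This also stands. A reader might infer that the trial is underpowered because of loss; the article does not establish that. Nor does it say that the 15 % in the sample size was taken from the pilot: the values are equal, but the link is an inference.

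**The origin of 663 is not known.** It is tempting to say that 663 is exactly 442 × 1.5 and so certainly contains no loss. But 442 is 442.9 truncated, and the 80 % power route reaches 663.4. The article supports only the weaker statement that the loss or the power is misstated.

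**The 79 % figure is one reading.** It treats the 15 % and the 8 % as two successive losses after inclusion. The article does not define attrition as separate from loss to follow-up, and the two may be a garbled account of one allowance. The figure should not set the severity.

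**Practical consequence is limited.** Inclusion ended in July 2016, and the Discussion says recruitment stopped at 12 months even where centres were short of their numbers. Achieved numbers will decide precision. That lowers the severity but leaves the published justification wrong. Multiple imputation of the primary endpoint might recover some information, but the Sample size section claims no credit for it.

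**Conclusion.** The point holds as an internal arithmetic error of moderate severity. The stated inputs require about 776 to 782 patients per arm per indication, not 663, so the paragraph misstates either what 663 contains or the power that it gives. The 720 enrolled delivers 85 % power only if total loss is about 8 %. At the article's own 15 % the power is about 82 %, a shortfall of about 3 points.

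This rests on the normal approximation, a design effect held at 1.5, no recovery of information through imputation, and 720 actually enrolled in each arm for each indication. It makes no allowance for there being only six centres. It does not show that the trial itself lost power through attrition, because loss after inclusion is not reported separately.

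**What to change.** Correct the sample-size paragraph wherever the justification is next reported:

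- Restate 663 as the evaluable number per arm per indication after the design effect, with no loss included. The authors should check this against their original calculation; if that used 80 % power with a 15 % mark-up, the stated power is the item to correct.
- State that 720 enrolled allows for about 8 % loss in total.
- Report the power as about 82 % at 15 % loss and a design effect of 1.5. Quote 79 % only if the 15 % and the 8 % really are separate losses.
- Say what the 15 % and the 8 % each measure, and count only loss after inclusion. The pilot's 15 % can inform this only if its refusals and its losses to follow-up are reported separately; the article does not give that split.

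The cost is a change of text and, if the pilot is used, one tabulation of existing pilot data. Enrolment, the endpoint and the analysis model do not change.

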### Statistical analyses

Analyses will be intent-to-treat (ITT). Any missing values for the primary endpoint will be computed by the multiple imputation method. In which case, the robustness of the conclusions made on observed cases will be verified and a possible discrepancy will be analysed based on any biases in data collection that may have been identified.

Descriptive analyses will provide the following information for each continuous variable: mean value, standard deviation, 95 % confidence intervals (95 % CI), minimum, 1st quartile, median, 3rd quartile and maximum, and number of missing observations. Categorical variables will be summarised in frequency tables (with 95 % CI). Intracluster correlation coefficients will be calculated.

The primary endpoint will be tested using the Generalised Estimating Equations model, account being taken of the cluster trial design. Secondary continuous endpoints will be analysed with a mixed-model ANOVA including a random centre effect. For categorical variables, treatment effect will be tested using the Generalised Estimating Equations model, account being taken of the cluster trial design. All tests will be two-tailed with a 5 % alpha risk. All statistical tests will be performed using SAS version 9.2 software.

The health economic analysis will consider total cost, hospital costs, ambulatory costs, cost borne by the family and costs to society. Analysis of management costs in both study arms will be ITT. Cost comparisons will be performed using appropriate statistical methods after determining the type of distribution (normal, log normal or beta).

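### The assurance of enough power for season, time-of-day and weekend subgroups does not hold on the per-indication basis on which the trial is sized: a 10-point treatment-by-subgroup interaction has about 27–48% power

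*Protocol article*

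**What the plan says.** The Sample size section sets every quantity for each indication. It expects that "our primary endpoint) will be 50 % in the control group" and aims for an "absolute reduction of at least 10 % (i.e. from 50 to 40 %) in the intervention arm for each indication (fever/gastroenteritis". It assumes a "relatively low weak design effect due to cluster randomisation (about 1.5") and arrives at "a sample size of 663 patients/arm/indication will be required for 85 % power and a 5 % alpha risk". It then allows for an "attrition rate of about 8 %, 720 patients will be required (1440/indication, i.e. a total of 2880 patients").

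The next sentence is the one at issue: "This sample size should provide enough power and precision for subgroup analyses (season versus diurnal cycle, weekend versus weekdays"). It gives no subgroup effect, subgroup size or power figure. It does not say whether the target is the effect inside a stratum or the difference in effect between strata, nor whether fever and gastroenteritis are analysed separately or together.

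On testing, the Statistical analyses section says: "All tests will be two-tailed with a 5 % alpha risk".

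**The concern.** A trial with 85% power for an overall effect has less than that for the same effect in any part of the sample. A difference in effect between two equal halves has four times the variance of the overall effect. Unless the sample was enlarged for the purpose, a general assurance of subgroup power cannot be right, and the stated sample size shows no such enlargement.

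The subgroup aim is not incidental. The Discussion says that recruitment stopped at 12 months so that seasonality could be examined, even where a centre was short of its target, and that two centres had trouble enrolling. The numbers available for subgroups may therefore be below plan. If the assurance stands, a reader could take a non-significant season or weekend comparison as evidence of equal effect, when the trial had little chance of seeing a difference.

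**Working it through.** **Inputs.** From Sample size: 50% vs 40% per indication, design effect (DE) 1.5, 85% power, 663 per arm per indication, 720 after 8% attrition, about 240 patients per centre per indication. From Statistical analyses: two-sided 5%. From Design: six centres, 1:1, so three per arm.

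**The plan's own figure.** The pooled-variance formula for two proportions without continuity correction gives 443 per arm. 443 × 1.5 = 664.5, against 663 stated, and 663/0.92 = 720.7, against 720 stated. So 663 is what the main comparison needs, with no reserve for subgroups. The match leaves out the loss that the text describes as "considering a loss of follow-up of 15" %. Because of this, I show a range of analysed patients per arm per indication: 612 (720 × 0.85), 663 and 720. Power for the main comparison at DE 1.5 is then 82.0%, 84.9% and 87.7%.

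**Subgroup shares.**
- Equal halves: f = 0.50, an illustration.
- Epidemic weeks: 8 × 10 = 80 against 4 × 42 = 168 per centre per indication, so f = 80/248 = 0.32. This comes from the document.
- Weekend: an assumption from the out-of-hours definition under Design. Weekday nights give 5 × 12 = 60 h, Saturday from 1 p.m. gives 19 h and Sunday 24 h. So f = 43/103 = 0.42 in a week without school holidays, if inclusions follow eligible hours.

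**Formulas (normal approximation).**
- Effect within a stratum: power of the two-proportion test for 50% vs 40% with N × f / DE per arm.
- Interaction: SE = √[0.49 × DE/N × (1/f + 1/(1−f))], where 0.49 = 0.5×0.5 + 0.4×0.6. Power = Φ(0.10/SE − 1.96).
- Interactions are shown at DE 1.5 and at DE 1.0, because centre effects may largely cancel when strata are compared within centres.

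For example, with N = 663, f = 0.5 and DE 1.5: SE = √(0.49 × 1.5/663 × 4) = 0.0666, so power = Φ(1.50 − 1.96) = 32%. With DE 1.0, SE = 0.0544 and power is 45%.

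**Results: power (%) at 612 / 663 / 720 per arm per indication.**

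| Target | Per indication | Both indications pooled (N doubled) |
|---|---|---|
| Effect in a half-size stratum, DE 1.5 | 52.8 / 56.1 / 59.6 | 82.0 / 84.9 / 87.7 |
| Effect in the weekend stratum (42%), DE 1.5 | 45.8 / 48.8 / 52.1 | 74.8 / 78.1 / 81.3 |
| Effect in the epidemic stratum (32%), DE 1.5 | 37.0 / 39.6 / 42.4 | 63.6 / 67.1 / 70.7 |
| Effect in the non-epidemic stratum (68%), DE 1.5 | 65.7 / 69.2 / 72.8 | 91.8 / 93.6 / 95.3 |
| 10-point interaction, 50/50, DE 1.5 | 30.3 / 32.3 / 34.6 | 53.2 / 56.5 / 60.0 |
| 10-point interaction, 50/50, DE 1.0 | 42.4 / 45.2 / 48.3 | 70.5 / 73.9 / 77.4 |
| 10-point interaction, 32/68, DE 1.5 | 27.1 / 28.9 / 31.0 | 47.9 / 51.0 / 54.3 |
| 10-point interaction, 32/68, DE 1.0 | 37.9 / 40.5 / 43.3 | 64.7 / 68.1 / 71.7 |

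**A smaller design effect in smaller strata.** DE 1.5 with 240 per centre implies an intracluster correlation of 0.5/239 = 0.0021. At N = 663, half a centre's patients number 110.5, so DE = 1 + 109.5 × 0.0021 = 1.23. Power in a half-size stratum is then 64.7% (62–68% over 612–720). That is still below 85%.

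**Detectable interaction.** (1.96 + 1.036) × SE at N = 663 with 85% power is 20.0 points (DE 1.5) or 16.3 points (DE 1.0) for equal subgroups. For the epidemic split it is 21.3 or 17.4 points. The main effect is 10 points.

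**The case against.** The best defence is pooling. The sentence follows directly on the total of 2880 patients, and season, time of day and weekend cut across both indications. Half of the pooled sample is as large as one indication's full sample, so the effect within a half-size pooled stratum has 82–88% power, and the larger non-epidemic stratum has more. This stands: a reader might infer that the claim fails on every reading, and it does not. But the article does not say that the indications are pooled, and its effect and sample size are set for each one. Nor does pooling rescue the epidemic stratum (64–71% at DE 1.5) or the interaction (48–77%).

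A reader might also take 30–45% as the power of any subgroup comparison in this trial. The document does not support that, because it fixes neither the type of comparison nor the population. That range belongs to a per-indication, 10-point interaction between roughly equal subgroups. Likewise, a weekend share of 2/7, the calendar share of days, is tempting but does not fit the out-of-hours definition, which puts it near 42%.

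Finally, nothing in the article says that a null subgroup result will be read as equal effect, and subgroup definitions and tests may properly be left to an analysis plan. Both points are fair. The finding concerns only the assurance that the article itself gives.

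**Conclusion.** The assurance is unsupported, and on the basis on which the trial is sized it is wrong. Per indication, none of the subgroup analyses examined reaches the planned 85%: about 27–48% for a 10-point interaction, and at design effect 1.5 about 53–60% within a half-size stratum, 46–52% at weekends and 37–42% in epidemic weeks. A 10-point interaction is already a generous target, since it means the full effect in one stratum and none in the other.

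The figures rest on the stated 50% vs 40% and design effect, on 612–720 analysed per arm per indication, on a weekend share that is my assumption, and on normal quantiles. With three centres per arm, a small-sample correction would lower the within-stratum figures further. The primary comparison and its sample size are not touched by this point.

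**What to change.** Withdraw the statement that the sample size gives enough power for subgroup analyses. In its place, say that these analyses are exploratory and will be reported as treatment-by-subgroup interaction estimates with confidence intervals. Give the interaction detectable with 85% power at 663 per arm per indication: about 16–20 points for equal subgroups and about 17–21 points for the epidemic split. If the assurance was meant for the pooled indications, say so, limit it to the effect within a stratum of at least half the patients, and note that it does not extend to the epidemic stratum or to interactions.

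The cost is a sentence or two and a weaker stated claim. Recruitment, data collection and the primary analysis do not change.
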